### Planned statistical analysis

#### Primary outcomes

A baseline comparison of demographics, length of stay in ICU, severity of illness, Acute Physiological and Chronic Health Evaluation score (APACHE II) on admission to ICU^45^ and baseline measures will be carried out between each group, using a combination of t tests and χ^2^ test.

Generalised estimating equations (GEE) will be used to compare the SF36 domain scores between groups and across time points. The GEE is a flexible technique that takes into account the correlations among individuals in longitudinal study designs and can account for missing data without a need for imputation techniques.^46^

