## Outcome measures

### Primary measure

The primary measure will be HRQoL as measured by the Short Form 36 health survey V.2 (SF36V.2)^38^ which demonstrates content and construct validity, sensitivity and responsiveness to change in many patient groups^39^ including ICU and postsepsis survivors.^40^ Pilot testing of the SF36 in this population by this team has been conducted in a current trial of inpatients postsepsis and has shown excellent completion rates at 6 months by telephone.^41^

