### Secondary measures

Patients’ readmission rates to hospital (medical record data), 12-month mortality (only expectedtrend) and economics and healthcare resource use. The latter will be monitored through examination of patient medical records, patient self-report and through Medicare/Pharmaceutical Benefits Scheme data extraction. The SF6D^42^ is a preference based six-dimensional health state measure suitable for economic evaluation that is derived from the SF36. The SF6D defines 249 health states, and a summary utility score for the SF6D will be calculated using UK weights.

Individual patient productivity will be measured using a work/activity impairment questionnaire, the Work Productivity and Activity Impairment Questionnaire (WPAI).^43^

The outcome measure of SF36V.2 will be taken at baseline, 6 and 12 months postenrolment in the study. All other measures (mortality, hospital readmission and economic and health resource use) will be taken at 6 and 12 months postenrolment.

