### Sample size

Power calculations are based on SF36 using previously published Minimally Clinically Important Differences (MCIDs) for the SF36 physical domain scores of 7.8 points (SD 15) in our pilot trial on rehabilitation in sepsis.^41^ The sample size, based on a two sample comparison of means was calculated at 78/group for the SF36 at 90% power with a two-sided, α error level of 0.05. Allowing for an almost 30% loss to follow-up (mortality, dropouts), a total of 204 participants will be required.^44^

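### The sample size is for one comparison of an SF36 physical score, but the primary analysis covers several SF36 domain scores and two follow-up times with no primary comparison named

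*Protocol article*

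**What the plan says.** All the relevant text is in the protocol article.

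- **Primary measure:** "The primary measure will be HRQoL as measured by the Short Form 36 health survey V.2 (SF36V.2"). No domain, summary score or time point is singled out.
- **Secondary measures** gives the schedule: "The outcome measure of SF36V.2 will be taken at baseline, 6 and 12 months postenrolment in the study". That makes two post-baseline assessments, neither ranked above the other.
- **Sample size** takes its difference from "SF36 physical domain scores of 7.8 points (SD 15) in our pilot trial on rehabilitation in sepsis" and continues: "The sample size, based on a two sample comparison of means was calculated at 78/group for the SF36 at 90% power", with a two-sided alpha of 0.05. No time point is given, and the physical domain scores are in the plural.
- **Planned statistical analysis, Primary outcomes:** "Generalised estimating equations (GEE) will be used to compare the SF36 domain scores between groups and across time points". The Abstract describes the analysis in the same way.

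No order of testing, adjustment for multiple tests or GEE term for the decisive test is stated. The Aims and Hypotheses ask only whether health-related quality of life improves.

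**The concern.** The power calculation and the primary analysis describe different tests. The first is one comparison of one score. The second is a set of comparisons, plural in score and spread over time, all placed under the heading for primary outcomes. The aim is framed as quality of life in general, so nothing in the article stops a significant result on any one domain from being read as the trial's positive answer.

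What is at stake is the meaning of the main result. A p-value below 0.05 on one of several unranked scores does not carry the 5% error rate given in the sample-size section. If the error rate is protected by splitting alpha, the 90% power in that section no longer applies.

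**Working it through.** **Inputs from the article.** Difference 7.8, SD 15, two-sided alpha 0.05, power 90%, 78 per group (Sample size); assessments at 6 and 12 months after baseline (Secondary measures).

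**Inputs assumed.** The article does not say how many domain scores are compared, so k = 2, 4 and 8 are shown. Correlation between scores runs from 0 to 0.7, and correlation between the two times is 0.6. Neither is in the article.

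**Step 1: reproduce the stated sample size.**
Standardised difference = 7.8/15 = 0.52.
n per group = 2 × (1.960 + 1.282)² / 0.52² = 77.7, rounded up to 78.
Power at 78 per group is 90.1% (normal) or 89.7% (t-test). The stated figure is correct for one test at 0.05.

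**Step 2: familywise error if each score is tested at 0.05.**
For k independent tests the chance of at least one false positive is 1 − 0.95^k:
- k = 2: 1 − 0.9025 = 9.75%
- k = 4: 1 − 0.8145 = 18.5%
- k = 8: 1 − 0.6634 = 33.7%

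For correlated scores, the test statistics were simulated under no effect (400,000 draws of multivariate normal vectors with equal correlation between scores):

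| Scores | Times tested separately | Correlation 0 | 0.3 | 0.5 | 0.7 |
|---|---|---|---|---|---|
| 2 | 1 | 9.8% | 9.5% | 9.0% | 8.4% |
| 4 | 1 | 18.5% | 17.5% | 15.5% | 12.9% |
| 8 | 1 | 33.6% | 29.9% | 25.0% | 19.0% |
| 8 | 2 | 51.9% | 47.1% | 40.0% | 31.2% |

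The one-time rows also describe a GEE that tests both times in one joint term per score. The last row applies only if 6 and 12 months are tested separately.

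**Step 3: power if alpha is split instead.**
With alpha/k per test, 78 per group and standardised difference 0.52, the noncentrality is 0.52 × √(78/2) = 3.247.

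| Tests | Alpha per test | Power (t-test) | Power (normal) | n per group for 90% (normal) |
|---|---|---|---|---|
| 1 | 0.05 | 89.7% | 90.1% | 78 |
| 2 | 0.025 | 83.6% | 84.3% | 92 |
| 4 | 0.0125 | 76.3% | 77.3% | 106 |
| 8 | 0.00625 | 68.2% | 69.6% | 120 |

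This is power for each comparison, assuming the same standardised difference on each score.

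**The case against.** Four objections deserve weight.

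1. **Multiplicity belongs in the analysis plan.** This is a condensed article and that plan is not shown. Testing order, adjustment and the exact model term may well be set there. A reader might infer that the trial has decided not to adjust. The article does not say so; it states no adjustment, which is a different thing. What remains is a mismatch between two things the article does state: a sample size for one comparison and a primary analysis of several.

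2. **The physical domain is the evident focus.** The sample-size section does point that way. But it uses the plural, gives no time point, and is not carried into the primary measure or the primary analysis. It shows intent without identifying the test.

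3. **A GEE handles the repeated measures.** One group or group-by-time term per score could cover both times, so counting each time as a separate test is only one reading. This objection stands for the time dimension, and for that reason the 31–52% figure is conditional. It does not remove multiplicity across scores.

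4. **The size depends on numbers not in the article.** This also stands. A reader might infer that the error rate is certainly several times 5%. That fits a family of about eight scores with any one significant result counting as success. With two scores at one time it is 8–10%, and the article states no success rule.

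**Conclusion.** The point holds in limited form. The stated primary analysis does not correspond to the single comparison that fixes alpha and power, and no primary comparison is named. On every reading with more than one score tested at 0.05, where any significant score can support the claim, the familywise error exceeds 5%. How far it exceeds 5% is a range, set by the assumed number of scores, the correlations and whether the two times are tested separately.

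It might be inferred that the error rate and the power both fail at once. They do not. Unadjusted testing keeps about 90% power for the comparison used in sizing and gives up the 5% familywise rate. Bonferroni keeps the 5% and gives up power for each comparison. The article's figures cannot both hold for the family, but each holds alone under one of these choices.

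Confidence is high that the designation is missing and the sections do not match. It is only moderate on the size, which rests on assumptions.

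**What to change.** Before unblinding, name one primary comparison and state it identically under Primary measure, Sample size and Primary outcomes: the between-group difference in one identified SF36 physical score, at one stated time point or as one stated GEE term. State which of the physical domain scores the 7.8-point difference and SD of 15 refer to; without that, the plural leaves the endpoint open.

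Six months is a reasonable time point because the clinic programme runs for up to 6 months after discharge, but the article ranks neither time, so the choice is the trial team's. The 95% contact rate reported from the current trial supports it only loosely, since that is dated from sepsis and this trial's assessments from enrolment.

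Make the remaining domains and the other time point secondary, either Holm-adjusted or reported as estimates with confidence intervals and no confirmatory claim. If the analysis plan or registry entry, neither seen here, words the endpoint differently, align them.

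The cost is a change of wording. With one comparison named, 78 per group at two-sided 0.05 and 90% power stands and no extra patients are needed on this account. The small downside is that the other domains lose primary status.

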### Randomisation

Participants will be randomised by opaque sealed envelopes after enrolment. Numbers on the envelopes will be generated by a computer-generated randomisation (http://www.randomization.com) table based on blocks of four to assign patients to either the intervention or the usual care group. The randomisation sequence will be concealed from consent designee staff and protected by an electronic password. Participants will be stratified based on a score >3 on the Cumulative Illness Rating Scale (CIRS-G).^29^

We are stratifying patients as most patients who develop sepsis syndromes have a number of comorbidities, but there can be a small number of relatively young, healthy patients who are affected. The allocation sequence will be generated by the research assistant attached to the trial. Patients will be consented by the chief investigator ([name]) and assigned to interventions by a second investigator (PT).

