### Methods for protecting against other sources of bias

This study will be double blinded with the assessors, data analysts and a number of investigators (TC, FC and GM) blinded from group allocation. There will be concealed allocation of participants. Participants will be stratified for CIRS-G.^29^ Participants when being consented will be told that they will be in one of the two groups which will be followed up posthospital and they may need to attend an outpatient clinic. Patients are unaware of the usual follow-up posthospital so should not feel they are receiving an increased/decreased level of care. Both groups will be contacted by telephone for completion of HRQoL life instruments at the required stages. Participants may have varying severity of illness, lengths of stay and/or time on mechanical ventilation in ICU; however, this will be compared between groups and if unequal adjusted models using the relevant covariates will be presented as well as unadjusted comparisons.

A few participants in either group may be referred to rehabilitation by their treating physician. This will be compared between groups. A number of patients may be uncontactable for final outcome measures; however, we have had a 95% rate in the current trial at 6 months postsepsis.^41^ The GEE^46^ will allow for missing data. If patients ‘cross-over’, that is, do not receive the planned intervention, they will still be analysed with the group they originally enrolled as per intention to treat.

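### GEE is relied on to deal with missing SF36 scores, but unweighted GEE is generally valid only when loss is completely at random, so health-related loss can bias the primary comparison

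*Protocol article*

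**What the plan says.** Under Primary measure, "The primary measure will be HRQoL as measured by the Short Form 36 health survey V.2". Under Planned statistical analysis, Primary outcomes, GEE "will be used to compare the SF36 domain scores between groups and across time points", and the technique "can account for missing data without a need for imputation techniques". Under Methods for protecting against other sources of bias, the protocol accepts that some patients will not be reached for the final measures and answers that GEE "will allow for missing data".

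Neither place states a missingness assumption, a weighting scheme or a working correlation. The Sample size section reads "Allowing for an almost 30% loss to follow-up (mortality, dropouts". SF36 is taken at baseline, 6 and 12 months. The bias section also says that both groups are telephoned for the quality-of-life instruments, that contact was 95% at 6 months in the team's current trial, and that models are adjusted for illness severity and similar covariates only if the groups turn out unequal. The Secondary outcomes section applies GEE to the SF6D utilities as well.

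**The concern.** That GEE can be computed on incomplete records does not make its estimates valid on them. Unweighted GEE is consistent in general only if scores are missing completely at random, or if loss depends only on covariates in the model. For continuous scores it approaches validity under missing at random (loss depending on scores already observed) when the working correlation is correct. A likelihood-based mixed model also needs no imputation and is valid under missing at random; the protocol's sentence credits GEE with that property without the conditions.

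After sepsis, loss through death and dropout is plausibly related to health, and predictors of loss are not routinely in the model because adjustment depends on observed imbalance. What is at stake is the group difference in the primary outcome: part of a 7.8-point effect could be lost (or, under other mechanisms, created), and the confidence interval would not show it.

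**Working it through.** **Inputs from the protocol.** The target difference is set "for the SF36 physical domain scores of 7.8 points (SD 15) in our pilot trial"; the size is "calculated at 78/group for the SF36 at 90% power with a two-sided, α error level of 0.05"; 204 in total; almost 30% loss; three visits.

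**Assumptions (not in the documents).** Within-patient correlations, how loss depends on health, and equal allocation.

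**1. The plan's own figures.** n per group = 2(1.960 + 1.282)² × 15² / 7.8² = 2 × 10.51 × 225 / 60.84 = 77.7, so 78. Then 78 × 1.30 = 101.4, so 102 per group and 204 in total. Both reproduce. Read as a share of those enrolled, the allowance is 1 − 156/204 = 23.5%; as worded it is about 30%. Both levels are used below.

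**2. Independence GEE, loss related to health in controls only.** With group-by-time terms, the 12-month estimate is the difference between mean observed scores. Let a control's 12-month score be missing with probability 1/(1 + exp(−(c − z))), where z is the standardised 6-month score and c is chosen to give the loss rate. Let the intervention arm lose the same share at random. Integrating over a standard normal z, the mean z among controls still observed is m = 0.2528 at 30% loss. Observed controls then look too well by SD × ρ × m, where ρ is the 6-to-12-month correlation:

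| ρ | 15 × ρ × 0.2528 | Estimate (truth 7.8) |
|---|---|---|
| 0.3 | 1.14 | 6.66 |
| 0.5 | 1.90 | 5.90 |
| 0.6 | 2.28 | 5.52 |
| 0.7 | 2.65 | 5.15 |

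Large simulations agree (6.66, 5.91 and 5.18 for ρ of 0.3, 0.5 and 0.7). At 23.5% loss and ρ = 0.6, the bias is −1.8.

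**3. Same mechanism at 30% loss, other working structures.**
- Exchangeable, and truly exchangeable: no bias, 7.8.
- Exchangeable, truth AR(1) with 0.7 between adjacent visits: bias −0.2, so 7.6.
- Exchangeable, true correlations 0.3 (baseline–6 months), 0.2 (baseline–12) and 0.6 (6–12): 6.7 to 6.9 across runs.
- Correct unstructured covariance: about 7.8.

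**4. Same mechanism in both arms, correlation 0.6.** With no true effect the bias is 0.0. With a true effect of 7.8, independence GEE is off by −0.6 (23.5% loss) to −0.7 (30%), because treated patients score higher and fewer are lost (25% against 35% at 30% overall). Correct exchangeable GEE is off by 0.0.

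**5. Smaller loss, controls only, true correlations 0.3/0.2/0.6.** At 10% loss, m = 0.091 and independence GEE gives 7.8 − 15 × 0.6 × 0.091 = 6.98; exchangeable GEE gives 7.4 to 7.5. At 5%, m = 0.047 and independence GEE gives 7.38; exchangeable gives 7.6 to 7.7.

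**6. Loss depending on the unseen 12-month score, controls only, correlation 0.6.** Bias is −3.0 to −3.8 with independence and −1.7 to −2.1 with the correct exchangeable structure. A mixed model with that same covariance solves the same equations for the means, so it would share the second bias. Only a sensitivity analysis addresses this case.

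**The case against.** The defence has real force on several points.

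- **The largest biases use independence GEE and control-only loss.** The protocol states neither. It describes GEE as allowing for correlation in longitudinal data, which points away from independence, and an article may leave the working structure to the analysis plan.
- **Both arms are telephoned alike for SF36.** A reader might infer that retention must differ because only the intervention arm attends the clinic. The documents do not support that; clinic contact could affect retention, but this is conjecture.
- **Contact was 95% at 6 months.** Missing scores among survivors may therefore be well below 30%. There is no 12-month figure, however, and the trial's own planning allowance is almost 30%.
- **Part of that 30% is death.** The Background cites 26% to 63% one-year mortality in long-stay ICU patients. The documents give no split, and no missing-data model recovers a score after death.
- **GEE can be repaired rather than replaced.** In the 30% control-only setting with correlations 0.3/0.2/0.6, GEE with an unstructured working correlation gave 7.69.

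These points limit the size of the problem; they do not rescue the sentence. It is a positive statement, made twice and without conditions, and the second time it serves as the bias protection. An analysis plan that followed it would see no need to do more. A reader might also infer that nothing will be done about missing data. That goes too far, since an analysis plan not shown here could add weighting or sensitivity analyses.

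**Conclusion.** The concern holds as a risk of bias, not as a demonstrated bias. The claim that GEE takes care of missing data is wrong without a missingness assumption and a suitable working correlation. With loss at the planned level and related to earlier health in one arm only, the 12-month difference could fall from 7.8 to about 5.2–6.7 (independence) or 6.7–7.8 (exchangeable), against about 7.8 with a correct unstructured covariance. With the same mechanism in both arms the bias is about 0 to −0.7; it is zero in the settings tried when there is no true effect or the working structure is correct. It shrinks further if loss among survivors is 5–10%.

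All these sizes rest on assumed correlations and loss mechanisms; only the SD, the difference and the loss allowance come from the protocol. The stronger reading, that illness-related loss does bias the primary result, is not supported: direction and size depend on facts that the documents do not give.

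**What to change.** - Analyse SF36 scores with a likelihood-based repeated-measures model: all three visits, group-by-time terms, unstructured covariance. Inverse-probability-weighted GEE, or GEE after multiple imputation, is an acceptable alternative. Treat the SF6D utilities consistently.
- Correct the sentence in Primary outcomes and the one in Methods for protecting against other sources of bias, so that each states the missing-at-random assumption on which the analysis rests.
- Add one delta-shift sensitivity analysis for patients who are alive but not contacted.
- State separately that SF36 scores after death are undefined, not missing, and that the SF36 comparison is to be read alongside mortality.

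The cost is revised wording and a little extra programming. No new data are needed.

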#### Secondary outcomes

Mortality will be compared between groups using a Cox proportional hazards (time until death) analysis.^47^ Time to first readmission will be compared between groups by a survival analysis. Utility estimates derived from the SF6D will be analysed using a GEE. Healthcare costs will be compared between groups using a generalised linear model to account for the non-normal distribution. Economic (health resource) evaluation will be a within-trial incremental cost utility analysis with a societal perspective.^48^ Direct costs included will be: cost of care provided in hospitals, by general practitioners, home nursing, complementary (allied) health providers, alternative health providers, opportunity cost of unpaid carers, cost of transportation to programme and to other health services and cost of pharmaceuticals. Indirect costs include loss of productivity due to disease, such as time lost from work or providing informal care to another individual. All costs will be valued using market costs where available and productivity costs will be valued using actual patient wage rates.

The subgroup of rural patients will be analysed in the full analysis and subgroup results will be compared with metropolitan patients.

#### Data management

A custom-designed database will store de-identified patient data on a secure password protected file. This will be entered from hard copies of the scoring sheets. Data will be reviewed by research office staff twice yearly and cross referenced with stored hard copies. A data management committee comprising a senior ICU specialist, a senior critical care nurse and a senior physiotherapist will review the data every 6 months.

#### Contingencies

If participant recruitment does not reach the required sample size in 2 years, the study can be extended for a further 1–2 years.

### Methods for protecting against other sources of bias

This study will be double blinded with the assessors, data analysts and a number of investigators (TC, FC and GM) blinded from group allocation. There will be concealed allocation of participants. Participants will be stratified for CIRS-G.^29^ Participants when being consented will be told that they will be in one of the two groups which will be followed up posthospital and they may need to attend an outpatient clinic. Patients are unaware of the usual follow-up posthospital so should not feel they are receiving an increased/decreased level of care. Both groups will be contacted by telephone for completion of HRQoL life instruments at the required stages. Participants may have varying severity of illness, lengths of stay and/or time on mechanical ventilation in ICU; however, this will be compared between groups and if unequal adjusted models using the relevant covariates will be presented as well as unadjusted comparisons.

A few participants in either group may be referred to rehabilitation by their treating physician. This will be compared between groups. A number of patients may be uncontactable for final outcome measures; however, we have had a 95% rate in the current trial at 6 months postsepsis.^41^ The GEE^46^ will allow for missing data. If patients ‘cross-over’, that is, do not receive the planned intervention, they will still be analysed with the group they originally enrolled as per intention to treat.

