## Methods/design

This is a prospective, double-blinded, interventional, repeated measures, superiority, randomised controlled trial with concealed allocation, blinded assessors and intention-to-treat analysis. The study has been designed in accordance with the Consolidated Standards for Reporting of Trials guidelines^27^ (figure 1) and the Standard Protocol items: Recommendation for Interventional Trials (SPIRIT 2013).^28^ The trial will be completed in two outpatient clinics. One clinic will be in the outpatient department located at the university-affiliated tertiary hospital Royal Brisbane and Women’s Hospital (RBWH), Brisbane, Australia; the other will be located at a regional hospital—the Bundaberg Base Hospital, Bundaberg, Queensland, Australia.

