## Intervention

### Intervention group

Patients in the intervention group will attend a follow-up clinic two monthly for up to 6 months after discharge from the hospital. Screening instruments will be utilised on the first visit and appropriate management and referral provided. These will involve: overall medical review involving all systems assessment, medications, vital signs, physical activity assessment, muscle strength,^30^ assessment of mobility (*modified Rivermead Mobility Index*),^31^ balance assessment (*Berg Balance measure*),^32^ discussion with carer as to concerns (*Zarit Burden Interview*),^33^ screening for chronic pain syndromes (*Brief Pain Inventory*),^34^ nutritional review, screening with the (*PTSD*) *Checklist-Civilian Version* (for post-traumatic stress syndrome),^35^
*generalised anxiety disorder (GAD-7*)^36^ and *The Patient Health Questionnaire-9 for depression.*^37^ Following the results of the screening and team discussion, participants and/or carer will be referred to appropriate agencies including the general practitioner, specialist, physiotherapist, nutritionist, speech pathologist, exercise physiologist, psychologist and/or occupational therapist. These instruments are screens for post-ICU problems that have been identified in previous studies.^13–20^ Members of the research team include an intensivist/thoracic physician, two specialist respiratory physiotherapists, a psychologist, a senior nurse researcher, a professor of community and general practice and a health economist/community physiotherapist. This individualised management is in line with recommendations of the NICE clinical guidelines.^8^

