### Standard care

Patients in the control group will have usual care, that is, they will be referred to specialist outpatient clinics and/or general practitioners on discharge.

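### The trial is labelled double-blinded, but participants are not blinded to the care they receive and they report the SF-36 primary outcome themselves

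*Protocol article*

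**What the plan says.** The article's title uses the term double-blinded, and Methods/design repeats it: "This is a prospective, double-blinded, interventional, repeated measures, superiority, randomised controlled trial with concealed allocation, blinded assessors and intention-to-treat analysis". The section Methods for protecting against other sources of bias gives the detail: "This study will be double blinded with the assessors, data analysts and a number of investigators", with three investigators then identified by initials.

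On the patient's side, that section says participants are told at consent that "they will be in one of the two groups which will be followed up posthospital and they may need to attend an outpatient clinic". It then argues: "Patients are unaware of the usual follow-up posthospital so should not feel they are receiving an increased/decreased level of care".

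The care differs visibly between arms. Under Intervention group: "Patients in the intervention group will attend a follow-up clinic two monthly for up to 6 months after discharge from the hospital", with extensive screening and onward referral. Under Standard care, control patients have usual care, meaning that "they will be referred to specialist outpatient clinics and/or general practitioners on discharge".

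On the outcome, Primary measure states: "The primary measure will be HRQoL as measured by the Short Form 36 health survey V.2". The bias section says the quality-of-life instruments are completed by telephone in both groups. Secondary measures adds the SF-6D, which is derived from the SF-36, and the WPAI questionnaire.

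**The concern.** In a trial whose primary outcome is self-reported, readers take double-blinded to mean that the person giving the answers did not know the treatment. The plan's own list of blinded roles does not include that person. A patient who has been through several visits to a multidisciplinary clinic knows what care was given. A patient who feels looked after, or who expects benefit, may rate health more favourably for that reason alone.

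A telephone assessor who does not know the arm cannot correct this, because the assessor only records the patient's rating. The SF-6D and the WPAI are exposed in the same way, so the bias would also carry into the utilities used in the economic evaluation.

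At stake is how a positive SF-36 result is read. Under the present label it would be credited with a protection that the design does not have for that outcome. The limitations listed at the front of the article name only the single-centre setting.

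**Working it through.** **Setting the sections side by side**

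| Role | Status in the plan | Bias this bears on |
|---|---|---|
| Staff obtaining consent | allocation sequence concealed (Randomisation) | selection |
| Telephone assessors | blinded | interviewer |
| Data analysts | blinded | analysis |
| Some investigators | blinded; others by implication not | varies with role |
| Clinic staff | not listed; they deliver the intervention | performance |
| Participants | not listed; they attend the clinic or have usual care | expectation and attention effects in SF-36, SF-6D and WPAI |

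The last row is the source of the primary outcome. The only safeguard offered there is the statement that patients do not know what usual follow-up is. The article describes no test of that assumption. Even if it is true, not knowing the usual level of care does not stop a patient from knowing that they attended a clinic.

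**The plan's own figure for the affected outcome**

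Inputs from Sample size: difference 7.8, SD 15, two-sided alpha 0.05, power 90%.

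n per group = 2 × (1.960 + 1.282)² × 15² / 7.8² = 2 × 10.51 × 225 / 60.84 ≈ 77.7, so 78. This agrees with the plan. Power at 78 per group is 90.1%. A t-based calculation gives 78.7, so 79, which is close enough.

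**What a response bias would do, for illustration only**

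The documents give no size for any response bias, so b below is an assumption, shown over a range that includes zero. The true effect is set to 0.

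SE = 15 × √(2/78) = 2.40

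P(p<0.05) = Φ(b/SE − 1.96) + Φ(−b/SE − 1.96)

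| Assumed bias b (points) | b as share of 7.8 | b/SE | P(p<0.05) |
|---|---|---|---|
| 0 | 0% | 0 | 5% |
| 1 | 13% | 0.42 | 7% |
| 2 | 26% | 0.83 | 13% |
| 3 | 38% | 1.25 | 24% |

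If the full 30% were lost from 102 per group (204/2), about 71 would remain (102 × 0.70 = 71.4). The SE would then be 15 × √(2/71) = 2.52, and biases of 2 and 3 points would give about 12.5% and 22%. The picture does not depend on which of these group sizes is used.

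**The case against.** The strongest reply is that the plan does not hide the arrangement. It says who is blinded, does not list participants, and by writing of a number of investigators concedes that others are not blinded. Anyone who reads the bias section can see the true position, so the fault lies in a label. That is largely right, and it limits the point. A reader might infer that blinding here is empty and protects nothing. The documents do not support that, because concealed allocation, blinded assessors and blinded analysts each guard against a real bias.

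A second reply is that patients are partly masked. Both groups hear the same consent wording and receive the same telephone contact, and control patients may attend specialist outpatient clinics too. A reader might infer that attending a clinic, or not, reveals the allocation in every case. That does not follow: knowing what care one receives is not the same as knowing that it is the experimental arm. The masking is still incomplete, since a two-monthly clinic with this much screening is conspicuous, and an attention effect does not require the patient to know which arm is experimental.

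Third, no bias has been shown. This stands. The table gives the consequence of an assumed bias and is no evidence that this trial has one.

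Fourth, an open clinic is probably unavoidable, and a call script is an operational detail that an article may leave to the full protocol. Both stand. No redesign is asked for, and the absence of a script from the article is not counted as a fault.

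**Conclusion.** The point holds as one of labelling and interpretation. By the article's own account the trial is assessor- and analyst-blinded. Participants know what care they receive, are at most partly masked to which arm is experimental, and supply the primary outcome and two related measures. The SF-36 comparison therefore stays open to response bias, and the assurance that patients will not sense a difference in care is an untested assumption.

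The size cannot be fixed from the documents. Under the plan's SD of 15 and 78 per group, a bias well below the 7.8-point target would matter: 3 points, if present, would raise the chance of a significant result under no true effect from 5% to about 24%, while 1 point would raise it only to about 7%.

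It may be tempting to lean on mortality and readmission as outcomes free of patient report. They add little as a check. Both are already secondary outcomes, only a trend is expected for mortality, and a clinic could improve quality of life without changing either.

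**What to change.** 1. In the title, Methods/design and the bias section, replace double-blinded with: assessor- and analyst-blinded; participants and clinic staff not blinded.
2. Add to the limitations that the primary outcome is self-reported under open care, and carry this into the interpretation of any SF-36, SF-6D or WPAI difference. Present the sentence about patients not sensing a difference in care as an assumption.
3. To protect the assessor blinding that the plan does claim, open each telephone call by asking the patient not to mention clinic visits, and record afterwards whether allocation was revealed. This step does not reduce expectation effects in the patient's answers; only the limitation statement deals with those.

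The cost is wording, one item on the call form and loss of the double-blinded label. Design, sample size and analysis are unchanged.
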